#### Usual Care (Control Group)

Participants in the control group will continue to receive their usual care for the duration of the study and will be reassessed. Usual care includes a range of therapies (e.g., physiotherapy or occupational therapy) provided by the hospital services. After the post-intervention assessment (3 months after the intervention), participants in this group will have the opportunity to attend the same program sessions if they wish.

### 2.5. Harms

Potential risks will be assessed prior to the start of the study and monitored continuously throughout the trial. Any adverse events, particularly serious or unexpected ones, will be documented by the research team in accordance with standard protocols and reported to the ethics committee. Safety monitoring will apply to both study groups, ensuring that any unintended effects are identified and addressed appropriately.

### 2.6. Outcome Measures

#### 2.6.1. Sociodemographic, Clinical, and Anthropometric Data

A structured baseline questionnaire will be administered to collect sociodemographic (age, sex, school type), clinical (primary diagnosis, years since diagnosis, laterality, current therapies, comorbid conditions), and anthropometric data (height and weight to calculate BMI in kg/m^2^). Additional screening items will assess levels of consciousness and orientation, potential contraindications for physical activity, prescribed medications, and relevant comorbidities (e.g., epilepsy, asthma).

#### 2.6.2. Pediatric Quality of Life Inventory (PedsQL)

A 23-item questionnaire that quantifies health-related quality of life across four domains (physical, emotional, social, and school). Scores for each domain and the total scale are the mean of item responses, with higher values indicating better quality of life. Participants self-report; parents provide proxy ratings for younger participants. The PedsQL shows good reliability and validity in cohorts with ABI, brain tumors, and traumatic brain injury [27].

#### 2.6.3. Child and Adolescent Scale of Participation (CASP)

A 20-item scale that rates participation in home, school, and community settings on a four-point Likert scale. Scores are expressed as a percentage of full participation; lower percentages indicate greater restriction. The CASP has been validated and widely used in intervention studies involving pediatric ABI [28].

#### 2.6.4. Global Physical Activity Questionnaire (GPAQ)

A 19-item instrument that captures moderate- and vigorous-intensity physical activity undertaken at work, during transport, and in leisure. Minutes per day in each intensity band are converted to metabolic-equivalent minutes to yield a total physical-activity score. The GPAQ demonstrates acceptable test–retest reliability and low-to-moderate criterion validity versus accelerometry in pediatric samples [29].

#### 2.6.5. Bruininks–Oseretsky Test of Motor Proficiency, Second Edition (BOT-2)

A test of gross motor proficiency through five subtests: bilateral coordination, balance, running speed and agility, upper-limb coordination, and strength. Raw scores are converted into scaled scores and composite scores for each motor domain and total score. The BOT-2 demonstrates high test–retest reliability and has been validated in pediatric populations with brain tumors, traumatic brain injury, and developmental coordination disorder [30].

### 2.7. Study Timeline

Participants will undergo baseline assessments prior to randomization, followed by a second evaluation at the end of the 3-month intervention period (completion). The full study timeline is detailed in Table 3.

### 2.8. Sample Size

The sample size estimation was based on the PedsQL, a validated outcome measure in pediatric neurological populations, including brain injury. Varni et al. (2006) reported standard deviations of approximately 10–11 points in cerebral palsy [31]. Assuming an SD of 10 points, with a two-sided alpha level of 0.05 and statistical power of 80%, the calculated sample size to detect a between-group difference is approximately 39 participants per group. Adjusting for an anticipated attrition rate of 15%, the final sample size was set at 45 participants per group.

### 2.9. Data Management and Monitoring

Data will be collected electronically using a secure, encrypted online database designed for each phase of the study, including eligibility screening and pre- and post-intervention assessments. No personally identifiable information will be stored in the database. Each participant will be assigned a unique identification code, generated through a random number sequence and stored separately in an independent table, ensuring a pseudonymized process. Data access will be limited to a secure hospital computer, with only the main investigators authorized to retrieve or manage the information. This system safeguards confidentiality and ensures protocol compliance.

### 2.10. Statistical Methods

The comparability of the study groups will be assessed by the similarity of the distribution of the variables of interest at baseline. The analysis will follow standard methods for randomized controlled trials, using two-group comparisons for all participants on an intention-to-treat basis. The chi-squared test or Fisher’s exact test will be used to compare proportions. Student’s t-test will be used to compare means between groups with normally distributed data. The Mann–Whitney test will be used to compare quantitative variables between groups in the case of a non-normal distribution, as determined by the Kolmogorov–Smirnov test. Correlations between quantitative measures will be determined by Spearman’s rho correlation coefficient. Matched pair data analysis is also calculated. In addition, multivariate analysis will be performed using multiple linear regression and logistic regression, depending on the response under consideration. This will allow for adjustment of the effectiveness of the intervention for potential confounders and the identification of other variables associated with each of the outcomes. Statistical significance will be set at ≤0.05. Data will be analyzed using the Statistical Package for the Social Sciences (SPSS) software, version 27.0 (IBM Corp, Armonk, New York, NY, USA).

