### 2.1. Trial Design and Setting

The study protocol describes the methods for a controlled trial with two parallel groups. The trial will compare the effectiveness of a sport-based exercise program in combination with usual care (experimental group), versus usual care alone (control group) in adolescents with ABI. The study screening, intervention, and assessments will be carried out at a pediatric hospital in Madrid, Spain, called Niño Jesús Hospital.

A flowchart of the study design according to the CONSORT guidelines is shown in Figure 1.

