## Figures and Tables

**Figure 1 jcm-14-05970-f001:**
[figure not shown]
Flowchart.

**Table 1 jcm-14-05970-t001:** Eligibility criteria.

Inclusion Criteria	Exclusion Criteria
Be aged <18 years at study entry.	Do not have a completed and signed informed consent form.
Have a medical diagnosis of acquired brain injury in the subacute or chronic stage.	Have medical comorbidities that contraindicate safe exercise (e.g., cardiac or respiratory instability, and uncontrolled seizures).
Be able to understand simple instructions from the program.	Failure to cooperate during the preliminary tests of the program.

**Table 2 jcm-14-05970-t002:** Template for intervention description and replication checklist for the intervention.

Items	Description of Items
Name of the intervention for the experimental/comparison group	Experimental group: sport-based exercise program and usual care sessions. Control group: usual care sessions.
Rationale	
Materials used in the intervention	Experimental group: The program is centered around different sports disciplines, which are adapted to participants’ functional condition, as well as different generic equipment, such as balls, chairs, tables, and platforms, among others.
Intervention procedures	Experimental group: The content of this program is designed around a sport-based framework incorporating motor patterns and task demands from various sports disciplines. It uses a circuit format to promote functional movement, progressive task complexity, and social interaction in small groups tailored by age and functional ability. Group composition will consider motor proficiency, cognitive, and behavioral profiles to balance skill levels and promote peer support. Strategies such as individualized task modification, use of visual and verbal cues, and structured routines will support engagement. Control group: Usual care encompasses a range of therapies (e.g., occupational therapy, physiotherapy, psychological support) provided by the rehabilitation services within the center. Typical frequency is 2–3 sessions per week, mainly individual or small group-based, and does not routinely include sport-based or structured group exercise. Following the post-intervention assessment, participants from this control group can participate in the same program sessions upon request.

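### Section 2.10 adds a matched-pair analysis under the common 0.05 threshold without a stated role; a test on pre-post pairs addresses change over time, not the programme's effect (minor)

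*Protocol article*

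**What the plan says.** Section 2.10 of the protocol article bases the analysis on "using two-group comparisons for all participants on an intention-to-treat basis". It then names chi-squared or Fisher tests for proportions, Student's t or Mann–Whitney tests for quantitative outcomes, and Spearman correlations. Next comes "Matched pair data analysis is also calculated". Multiple linear and logistic regression follow, to adjust the intervention effect for potential confounders. The paragraph closes with a single threshold, "Statistical significance will be set at ≤0.05", and exempts no test from it.

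The paired sentence does not say what is paired with what, in which arm, for which outcome or for what purpose.

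Other sections show what pairs exist:

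- Section 2.1 describes two parallel groups, the programme plus usual care against usual care alone.
- Section 2.3 allocates participants 1:1 by stratified block randomisation, with no matching of individuals across arms.
- Section 2.7 sets two assessments, at baseline and at the end of the three-month period.
- Section 2.4 has therapies such as physiotherapy and occupational therapy continuing in both arms.
- Table 1 admits patients who "Have a medical diagnosis of acquired brain injury in the subacute or chronic stage".

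**The concern.** The trial asks whether adding the programme to usual care gives a better result than usual care alone. A paired test on baseline and completion scores has a different null hypothesis, that the mean change over three months is zero. That null is false whenever participants change for any reason: natural recovery, usual therapy, practice on the motor test, growth or regression to the mean. Subacute injuries are eligible and both arms keep receiving rehabilitation, so some change without a programme effect is plausible. The document gives no rate for it.

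The paired analysis stands beside the between-group tests under the same threshold, with nothing to mark it as descriptive. At reporting, a significant pre-post improvement in the experimental arm could be presented as support for the programme. So could significance in the experimental arm next to non-significance in the control arm. Neither pattern tests a difference between arms, and the randomised control would not protect a conclusion drawn that way.

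**Working it through.** **Which pairs are possible.** Individuals are not matched across arms (sections 2.1 and 2.3), and each is assessed twice (section 2.7). The only pairs in the design are a participant's own two scores. That the test would be run within each arm is an inference. If the pairs were pooled over both arms, the null would still be zero change over time.

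**Sample size used.** Section 2.8 gives about 39 per group before attrition, 15% attrition and 45 per group. The 39 cannot be rebuilt, because no between-group difference is stated; at SD 10, two-sided alpha 0.05 and 80% power it corresponds to about 6.3 to 6.4 points. That does not affect this point. For attrition, 39 × 1.15 = 44.85, which rounds to 45, while 39 / 0.85 = 45.9. Completers per arm are 45 × 0.85 = 38.25, taken as 38.

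**Assumptions not in the document.** No programme effect; the same mean change c in both arms, 0 to 0.4 SD; pre-post correlation r of 0.5 or 0.7; normal scores with equal SD at both visits.

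**Formula.** In SD units, the SD of change is √(2(1 − r)): 1.000 at r = 0.5 and 0.775 at r = 0.7. The paired t statistic is noncentral t with 37 degrees of freedom and noncentrality c√38 / √(2(1 − r)). The two-sided 5% critical value is 2.026. With p the rejection probability in one arm, and independent arms with equal recovery, the chance of significance in the experimental arm only is p(1 − p).

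Example: c = 0.2, r = 0.5 gives noncentrality 0.2 × 6.164 = 1.233 and p = 0.225. Then p(1 − p) = 0.225 × 0.775 = 0.174.

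| Common change (SD) | Paired test significant, r = 0.5 | r = 0.7 | Experimental arm only, r = 0.5 | r = 0.7 |
|---|---|---|---|---|
| 0 | 5.0% | 5.0% | 4.8% | 4.8% |
| 0.1 | 9.2% | 12.1% | 8.4% | 10.7% |
| 0.2 | 22.5% | 34.1% | 17.4% | 22.5% |
| 0.3 | 43.7% | 64.3% | 24.6% | 23.0% |
| 0.4 | 67.1% | 87.3% | 22.1% | 11.1% |

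**Checks.** Simulation (20,000 trials per scenario, 38 per arm) agrees: at 0.2 SD the paired test rejected in 22.7% and 34.3%, and the experimental-arm-only pattern at 0.2 to 0.3 SD occurred in 17.7% to 24.9%. A separate calculation with 39 per arm and SD 10 gave 23% to 35% for a common change of 2 points and 45% to 65% for 3 points, over the same correlations.

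**Between-group test under the same conditions.** In simulation the two-sample t-test rejected in about 5% of trials throughout: 4.8% to 5.1% on change (38 per arm, r = 0.5) and 4.8% to 5.4% on the completion score (39 per arm).

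**The case against.** The strongest reply is that the plan already rests inference on the randomised comparison. Section 2.10 opens with it, section 2.8 sizes the trial for a between-group difference, and the regression is there to adjust the effect of the intervention. The paired sentence is an addition, and the Spearman correlations sit under the same threshold without being efficacy tests. A paired analysis is not wrong for its own question, and it could turn out to be no more than a mean change with an interval. Ranking supplementary analyses is often left to a fuller document.

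Most of this stands. The rates of 9% to 87% are not a fault of the paired test. They are its power to detect change that the calculation puts in, and with no change it rejects at 5%. They become false signals of efficacy only if change over time is presented as an effect of the programme. The recovery and correlation are assumed, and a mainly chronic case mix could make the recovery small.

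A reader might infer that the trial will judge efficacy from within-arm tests, or that its false-positive rate is inflated as planned. The document supports neither: it does not say that paired results decide anything, and the between-group test holds its level.

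The reply does not remove the whole point. The paired analysis is something the plan states, not a detail left out. It is listed among tests governed by one threshold, and a p-value from it cannot answer the question in section 2.1.

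**Conclusion.** The point holds as a minor one. The plan states a matched-pair analysis under the common threshold with no role, and the only pairs in the design are pre-post scores, so a significance test on them would measure change over three months. The planned between-group intention-to-treat comparison is sound and needs no repair on this account.

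The harm is conditional on misreading. Its possible size, under the assumed equal recovery and correlations, runs from about 9% of trials at 0.1 SD to 87% at 0.4 SD for a significant experimental arm. Significance in that arm only occurs in about 17% to 25% at 0.2 to 0.3 SD. The size depends entirely on those assumptions. That the paired test addresses a different null does not.

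**What to change.** Replace the matched-pair sentence in section 2.10 with wording such as: *Change from baseline will be summarised by arm descriptively (mean change with 95% confidence interval). Conclusions about the programme will rest only on the between-group comparison, using the planned linear regression of the completion score on arm and baseline score.*

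Linear regression is already in section 2.10; the new wording names the baseline score as a covariate, which the section does not do. It also gives the baseline measurements a proper inferential use through the randomised contrast.

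The cost is one sentence, with no extra data, participants or follow-up. What is given up is the within-arm p-values, which do not answer the trial's question; the within-arm changes are still reported.

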Furthermore, participation in group-based exercise sessions tailored to each participant’s developmental stage and interests promotes peer interaction, self-esteem, and social engagement—factors especially relevant for adolescents who frequently experience isolation and reduced physical activity participation [21,22,23,24]. This approach also enhances intrinsic motivation, facilitating long-term adherence to active, socially integrated lifestyles, reinforcing gains across multiple ICF domains [22,23,24]. However, despite these potential benefits, there remains a lack of standardized and replicable sport-based protocols specifically designed for adolescents with ABI that explicitly integrate the ICF framework—particularly those linked to psychosocial well-being.

Therefore, the aim of the present study is to design and evaluate a sport-based exercise intervention tailored to the specific needs of adolescents with ABI. The program is tailored to the developmental characteristics and functional needs of this population, with the goal of promoting improvements in quality of life, social participation, motor function, and physical activity engagement.

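### No outcome is named as primary: four outcomes share one 0.05 threshold with no hierarchy, although the trial is sized on the PedsQL alone

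*Protocol article*

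**What the plan says.** The aim at the end of section 1 describes a programme "with the goal of promoting improvements in quality of life, social participation, motor function, and physical activity engagement". The abstract, sections 2.6.2 to 2.6.5 and Table 3 cover the same four constructs, measured by the PedsQL, CASP, GPAQ and BOT-2, and none of these places gives one construct priority. In the article as shown, the word primary is attached only to diagnosis, never to an outcome.

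Section 2.10 plans two-group comparisons, paired analyses and adjusted regression models for the outcomes. The only decision rule is "Statistical significance will be set at ≤0.05". No ordering of outcomes or adjustment for their number accompanies it.

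The one sign of priority is in section 2.8: "The sample size estimation was based on the PedsQL", "with a two-sided alpha level of 0.05 and statistical power of 80" per cent. That section does not say whether the total or a domain score is meant. Section 2.6.2 defines four PedsQL domain scores and a total, and provides for parent ratings for younger participants. For the BOT-2, section 2.6.5 says "Raw scores are converted into scaled scores and composite scores for each motor domain and total score".

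**The concern.** A 0.05 threshold limits the false-positive risk of one test. It does not limit the risk of a conclusion that can rest on whichever of several tests succeeds. The article does not say which result carries the conclusion, so a significant CASP, GPAQ or BOT-2 result could be presented as showing effectiveness when the PedsQL, the only measure with a power calculation behind it, shows nothing. Nothing in section 2.10 rules that out. Accepting the PedsQL as primary by implication still leaves open which score, and whose rating, decides the trial. Once outcome data have been seen, that choice can no longer be credibly called prespecified.

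**Working it through.** **Inputs from the article.** Threshold 0.05 for every test (2.10); two-sided 0.05, 80% power, SD 10, 39 per group, 45 after attrition (2.8); four outcome constructs (sections 1 and 2.6); one post-baseline assessment (2.7). The article states no family-wise error rate, so there is none to reproduce.

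**Input assumed.** The correlation between the four test statistics. The article gives none, so a common value from 0 to 0.8 was used.

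**Step 1: four independent tests.**
- Any significant difference: 1 − (1 − 0.05)^4 = 1 − 0.8145 = 18.5%.
- A significant difference favouring the intervention: 1 − (1 − 0.025)^4 = 1 − 0.9037 = 9.6%. The single-test figure is 2.5%.

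**Step 2: correlated tests.** Four standard normal statistics, each √ρ × (shared component) + √(1 − ρ) × (own component), were simulated with no true effect, 2,000,000 draws per setting. A test counted as significant beyond 1.96.

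| Common correlation ρ | At least one significant difference | At least one favouring the intervention |
|---|---|---|
| 0 | 18.5% | 9.6% |
| 0.3 | 17.4% | 8.8% |
| 0.4 | 16.6% | 8.3% |
| 0.5 | 15.6% | 7.8% |
| 0.8 | 11.4% | 5.7% |

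The ranges are therefore about 11% to 19% for any difference and about 6% to 10% for a favourable one.

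**Step 3: what each repair does to the sample size.** Section 2.8 states "Assuming an SD of 10 points" and that "the calculated sample size to detect a between-group difference is approximately 39 participants per group", but not the size of that difference, so 39 cannot be reproduced directly. Solving backwards with the normal approximation:

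10 × (1.960 + 0.842) × √(2/39) = 6.34 points.

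This value is used only as an assumption for the comparison below.

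- *One primary outcome at two-sided 0.05.* The error rate for the main conclusion is 5%, the calculation in section 2.8 applies as it stands, and 45 per group is unchanged.
- *Four co-equal outcomes with Bonferroni.* Each is tested at 0.05/4 = 0.0125, and the family-wise rate under independence is 1 − (1 − 0.0125)^4 = 4.9%. For a 6.34-point PedsQL difference, power at 39 per group falls from 80% to about 62%. Restoring 80% needs 2 × 10² × (2.498 + 0.842)² / 6.34² ≈ 55.4, so 56 per group, or 56/0.85 ≈ 66 after 15% attrition.

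Naming one primary outcome needs no extra participants; keeping four co-equal ones would.

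**The case against.** The strongest reply is that the PedsQL is primary in all but name: the trial is sized on it alone, it comes first among the outcome instruments, and quality of life comes first in the aim. A condensed article may also leave multiplicity adjustment and the handling of sub-scores to an analysis plan that is not shown. Part of this stands. The absence of an adjustment method is not itself a fault here, and the PedsQL is the natural candidate. But basing a sample size on an instrument does not designate it as primary, and section 2.8 does not identify a score. Which outcome decides the trial is a design choice that an article with sections on outcomes, sample size and statistics would normally settle.

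It is also fair to say that the article contains no rule under which any single significant result counts as success. The error rates above are therefore conditional: they apply if the open choice is used that way.

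A reader might go further and draw three stronger conclusions that the article does not support.

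- *That every sub-score is tested at 0.05.* Counting five PedsQL scores, one CASP, one GPAQ and at least six BOT-2 scores gives 13, and 1 − 0.95^13 = 48.7%. Sections 2.6.2 and 2.6.5 define these scores, but section 2.10 never says that each is tested. Nor can the 13 be independent, since a total is built from the same material as its parts. At correlations of 0.5 and 0.8 the figure would be 33.4% and 19.2%.
- *That the risk is at least one in six.* For the four outcomes this holds only up to a correlation of about 0.4, so it is not a floor.
- *That this is the chance of a falsely favourable trial.* Counting only favourable results roughly halves the figures.

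**Conclusion.** The point holds as a failure to fix which outcome carries the conclusion, under a threshold that makes no distinction between outcomes. If any one of the four may support effectiveness, the chance of at least one false-positive difference is about 11% to 19%, and of at least one favouring the intervention about 6% to 10% against 2.5% for one test. Both ranges assume no true effect on any outcome and a common correlation between 0.8 and 0. Testing domain and subtest scores as well would raise them, by an amount that cannot be fixed from the article. The defect should be corrected before outcome data are seen; it does not invalidate the design or the sample size.

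**What to change.** Change sections 2.6, 2.8 and 2.10 together:

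1. Name the PedsQL total score at completion as the single primary outcome, tested at two-sided 0.05, and state in 2.8 that the sample size refers to that score.
2. Say which rater's score enters the primary analysis for participants who have parent proxy ratings under 2.6.2. Specifying self-report without addressing them would leave those participants unaccounted for.
3. State that the claim of effectiveness rests on this test alone.
4. Label the CASP, GPAQ, BOT-2 and all domain and subtest scores as secondary or exploratory, report them as estimates with 95% confidence intervals, and state that they cannot replace a null primary result. A Holm adjustment across the secondary outcomes is optional.

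This takes a few sentences and no additional participants. The small downside is that a secondary result, however strong, could not by itself support the effectiveness claim.
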